### Statistical analysis

A comprehensive statistical analysis will be performed using SPSS (IBM, USA) for the *a priori* hypotheses. Baseline characteristics will be reported as mean ± SD for normally distributed continuous variables, and as counts (percentages) for categorical variables. The Spearman correlation will be used to calculate the association between different biomarkers. A Cox proportional-hazards model will be used to examine the association between biomarker levels and outcomes. A value of *P* <0.05 will be considered statistically significant.

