#### Secretory Phospholipase A2

Secretory phospholipase A2 (sPLA2) and lipoprotein-associated phospholipase A2 (Lp-PLA2) are enzyme biomarkers of increased cardiovascular risk [74]. In addition, arachidonic acid release from membrane phospholipids by PLA2 is a key step in the control of eicosanoid. sPLA2 and Lp-PLA2 appear to be prospective candidates for inhibition [75]. High-dose atorvastatin significantly reduces sPLA2 and Lp-PLA2 mass and activity after acute coronary syndromes and mitigates the risk of death associated with sPLA2 mass. Atorvastatin may exert anti-inflammatory effects on phospholipases that contribute to its therapeutic benefit after acute coronary syndromes [74].

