### Markers of cardiovascular stress

Levels of MR-proANP, MR-proADM and CT-proET-1 will be determined using the Time-Resolved-Amplified-Cryptate-Emission (TRACE) technology on the Kryptor Compact analyzers (BRAHMS GmbH, Henningsdorf, Germany), from samples collected at the same time points as troponin.

T-pro-BNP levels will be measured using the Elecsys electrochemiluminescence immunoassay (ECLIA) proBNP II assay on a Roche Cobas E170 analyzer (Roche, Indianapolis, IN), from samples collected at the same time points as troponin. This assay uses two polyclonal antibodies that recognize epitopes located on the N-terminal part of pro-BNP. The lower limit of the detection range (sensitivity) is 5 pg/ml. Within-run coefficients of variation are 1.9% at a concentration of 64 pg/ml and 1.3% at 14,142 pg/ml. Total precision coefficients of variation are 3.1% at a concentration of 36 pg/ml and 2.7% at 125 pg/ml. Levels of the biomarkers of the renin-angiotensin pathway, including Ace2, will be measured.

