### Sample size calculation

We estimated that 200 patients (calculated sample size of 171) would be required to have a power of 0.90 (alpha = 0.05, two tail) to identify a difference(moderate effect size (f = 0.25) in PMI incidence between the 4 groups. (F test Anova:fixed effects,special,main effects and interactions; Analysis: a priori).

We plan to recruit 200 patients in total (50 in each treatment cell), providing an actual power of 0.94 to detect a moderate effect size.

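### The marker correlations and marker-outcome models take no account of randomised arm or sampling day, so on postoperative samples allocation can induce or distort associations between markers moved by the same drug, and between a marker and an outcome that drug changes

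*Protocol article*

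**What the plan says.** The Statistical analysis section names two association methods. For marker against marker: "The Spearman correlation will be used to calculate the association between different biomarkers". For marker against outcome: "A Cox proportional-hazards model will be used to examine the association between biomarker levels and outcomes". A P value below 0.05 "will be considered statistically significant". Neither sentence mentions the randomised arm, any covariate, or which sample is used.

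The stress markers are measured "from samples collected at the same time points as troponin", which the Troponin I section sets as preoperative and postoperative days 1 to 4. The section on markers of plaque burden has sPLA2 and Lp-PLA2 measured preoperatively and on day 2. Both drug protocols start treatment before surgery and continue it to discharge.

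The article expects the drugs to move these markers. The Secretory Phospholipase A2 section says "High-dose atorvastatin significantly reduces sPLA2 and Lp-PLA2 mass and activity after acute coronary syndromes". The Discussion postulates that ivabradine lowers NT-proBNP, MR-proANP, MR-proADM and CT-proET-1, that atorvastatin lowers sPLA2 and Lp-PLA2 mass, and that each drug lowers PMI. The Abstract makes the relation between markers and PMI an aim of the study.

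**The concern.** Half the patients are allocated to each drug. If a drug lowers two markers, treated patients tend to be low on both and untreated patients high on both. A correlation taken over everyone then appears even when the markers are unrelated within every arm. In the same way, a drug that lowers a marker and PMI makes the marker look related to PMI even if it carries no information about PMI among patients treated alike. If a drug lowers the marker but leaves the outcome alone, a real association is diluted.

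What is at stake is the mechanistic reading. The Discussion proposes that atorvastatin works through the phospholipases. A marker-outcome association taken across arms could seem to support that pathway when all it shows is that the drug changed both quantities.

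**Working it through.** **The plan's own figure.** The Sample size calculation says "We estimated that 200 patients (calculated sample size of 171" patients) "would be required to have a power of 0.90 (alpha = 0.05, two tail") at a "moderate effect size (f = 0.25"). For a fixed-effects F test with 1 numerator degree of freedom and four groups, the noncentrality is f² × N.
- At N = 171: 0.0625 × 171 = 10.69, with 167 denominator degrees of freedom. Power is 0.9015.
- At N = 200: 0.0625 × 200 = 12.5, with 196 denominator degrees of freedom. Power is 0.9404.

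Both the stated 171 and the stated 0.94 reproduce. For a factor split 1:1, f = d/2, so f = 0.25 means d = 0.5 SD. That effect size was set for PMI. It serves below only as a reference point for a moderate marker shift.

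**Inputs for the check.**
- From the article: N = 200, 50 per cell, 2x2 factorial, two-sided 0.05, and 52.9% PMI by troponin in the previous study cited in the Background.
- Assumed, because the article gives no figure: the marker shift d in within-arm SD units, and the PMI rate on drug (40% or 30%).

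**Two markers lowered by the same drug, independent within arm.** With half the patients treated, the between-arm covariance is d² × 0.5 × 0.5 = d²/4, and each marker's variance is 1 + d²/4. The induced correlation is therefore

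r = (d²/4) / (1 + d²/4).

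At d = 0.5 this is 0.0625/1.0625 = 0.059. At d = 1.0 it is 0.25/1.25 = 0.20. The two-sided 5% critical value of |r| at N = 200 is 0.139. Simulation with 4,000 runs per setting gave:

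| d (SD) | r, closed form | mean Spearman, all arms | rejected, all arms | rejected, arm-adjusted |
|---|---|---|---|---|
| 0 | 0 | 0.000 | 5.3% | 5.3% |
| 0.25 | 0.015 | 0.016 | 5.6% | 4.9% |
| 0.5 | 0.059 | 0.058 | 12.0% | 4.8% |
| 0.8 | 0.138 | 0.138 | 49.2% | 5.2% |
| 1.0 | 0.20 | 0.203 | 82.5% | 5.2% |
| 1.5 | 0.36 | 0.38 | 100% | 4.6% |

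The Monte Carlo standard error at 5% is √(0.05 × 0.95/4000) = 0.3 percentage points.

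**Two markers moved by different drugs.** The two allocations are orthogonal, so no correlation is induced. Over the same shifts the mean Spearman stayed within 0.002 of zero and rejection was 3.4% to 5.1%. Among six markers (four stress markers, and the two phospholipases counted once each) there are 15 pairs: 6 stress-stress, 1 phospholipase-phospholipase and 4 × 2 = 8 cross-drug. So 7 of the 15 pairs are exposed.

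**Marker and PMI, unrelated within arm, both lowered by one drug.** Logistic regression, 1,000 runs per setting, standard error at 5% of √(0.05 × 0.95/1000) = 0.7 percentage points:

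| d (SD) | PMI on drug | OR per SD, no arm term | rejected | OR with both indicators | rejected |
|---|---|---|---|---|---|
| 0.5 | 40% | 1.07 | 6.9% | 1.01 | 4.6% |
| 0.5 | 30% | 1.12 | 12.2% | 1.00 | 6.1% |
| 1.0 | 40% | 1.11 | 13.0% | 1.00 | 5.1% |
| 1.0 | 30% | 1.21 | 31.4% | 1.00 | 5.9% |

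**Dilution.** If the drug shifts the marker but not the outcome, a within-arm linear slope is multiplied by 1/(1 + d²/4) when arms are combined: 1/1.0625 = 0.94 at d = 0.5 and 1/1.25 = 0.80 at d = 1.0.

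**The case against.** The strongest objection is that the article is silent on arm. It nowhere says that arms or days will be pooled or that the Cox model will be unadjusted. An article condenses a fuller protocol, and covariates of secondary models are commonly left to an analysis plan that is not shown. A reader might infer that an unadjusted, pooled analysis has been fixed; the text does not support that. What remains is that an ordinary Spearman correlation is a two-variable statistic with no place for arm. Naming it alone for a randomised trial with mostly on-treatment samples fixes a method that a better one can replace at almost no cost.

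Other limits also stand:
- No marker effect size is given, so the high rates rest on assumed shifts near 1 SD. At 0.25 SD the inflation is negligible.
- Zero within-arm association is an unrealistic null for some pairs. The article describes both BNP and ANP as released in response to wall tension.
- The marker-PMI figures come from logistic regression. The Cox sentence refers to outcomes without naming PMI, and no model is named for marker against PMI. The figures illustrate the mechanism and do not measure the error rate of the Cox analysis.
- A reader might infer that the drugs were chosen because they move the markers. The Background justifies them mainly by heart-rate lowering and by prevention of plaque events. Marker reduction is a postulated mechanism.
- The preoperative sample escapes the problem only if it is drawn before the first dose. Both are placed within two hours of randomization, with no order stated.

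**Conclusion.** The point holds as a conditional one. If the stated analyses are run across all arms on postoperative samples, and the drugs act as the article postulates, allocation can induce or distort associations in two places: between markers moved by the same drug, and between a marker and any outcome that drug changes. For same-drug pairs with no within-arm association, the nominal 5% becomes about 6%, 12% and 83% at shifts of 0.25, 0.5 and 1.0 SD. For a marker and PMI it becomes about 7% to 31% over shifts of 0.5 to 1.0 SD and PMI of 40% to 30% on drug, against 52.9% off drug. All these shifts and on-drug rates are assumptions.

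It would go too far to say that spurious associations will arise, that every marker pair is affected, or that the trial's main result is at risk. Cross-drug pairs are unaffected under the postulated drug-specific effects, and the randomised primary comparison and the sample size do not depend on these analyses. The change is worth making because the correction is simple and restores the error rate to about 5%.

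**What to change.** In the Statistical analysis section, add for postoperative samples:

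1. Spearman correlations between markers are computed within sampling day and either stratified by arm or adjusted for it (partial Spearman).
2. Every model relating a postoperative marker to an outcome, the Cox model included, contains both treatment indicators (ivabradine yes/no, atorvastatin yes/no).

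This costs one or two sentences and a few degrees of freedom per analysis (two for the two indicators, three if their interaction is added). It needs no further patients, samples or assays. Postoperative markers need not be dropped from the prognostic analyses, since arm adjustment deals with the problem.

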## Discussion

Through this study, we postulate that ivabradine will reduce the rate and magnitude of PMI following emergent lower limb orthopedic surgery by reducing heart rate and attenuating catecholamine-induced tachycardia postoperatively. Secondly, we postulate that postoperative reduction in heart rate and catecholamine-induced tachycardia with ivabradine will correlate with a reduction in biomarkers of cardiovascular stress as measured by NT-proBNP, MR-proANP, MR-proADM and CT-proET-1, which will reduce atrial stretch and postoperative incidence of atrial fibrillation. We further postulate that atorvastatin will reduce the rate and magnitude of PMI following emergent lower limb orthopedic surgery via a reduction in sPLA2 and Lp-PLA2 mass.

To conclude, we aim to demonstrate that treatment with ivabradine and atorvastatin will cause a reduction in the incidence and magnitude of PMI, the benefit of which is derived primarily in patients with greater atherosclerotic burden as measured by higher CT coronary calcium scores.

## Trial status

This study is currently recruiting participants since 2012 and finishes once 200 patients are recruited.

## Abbreviations

Ace2: Angiotensin-converting enzyme 2
ADM: Adrenomedullin
ADP: Adenosine diphosphate
AF: Atrial fibrillation
ANP: Atrial natriuretic peptide
BNP: B-type natriuretic peptide
CAD: Coronary artery disease
CT: Computed tomography
CT-proET-1: Carboxy terminal fragment of ET-1
ECG: Electrocardiogram
ECLIA: Elecysys electrochemiluminescence immunoassay
ENOS: Endothelial nitric oxide synthase
ET-1: Endothelin-1
HDL: High-density lipoprotein
hs-CRP: High sensitivity C-reactive protein
HU: Hounsfield units
LDL: Low-density lipoprotein
Lp-PLA2: Lipoprotein-associated phospholipase A2
MR: Mid-regional fragments
NOF: Neck of femur
NT-proBNP: Aminoterminal fragment of prohormone B-type natriuretic peptide
PCI: Percutaneous coronary intervention
PMI: Perioperative myocardial infarction
sPLA2: Secretory phospholipase A2
TRACE: Time-resolved amplified cryptate emission.
